#### Further measurements

We assess sociodemographic data and profession-related variables (sex, work setting, years of professional experience) by a self-developed online questionnaire using the software Social Science Survey (SoSci Survey) (www.soscisurvey.de). Further measurements at different time points for physicians and SPs will be integrated in this study. However, because these outcomes are not the focus of the hypotheses of this study protocol, they will not be described further.

### Sample size

The sample size calculation is based on the main *hypothesis1* and the method of analysis. A review of the efficacy of non-web-based SDM interventions [54] including five RCTs described significant comparisons in two of the five studies. In the significant studies, effect sizes were calculated as *d* = 1.06 and *d* = 2.11. Taking the non-significant results into account, a conservative estimation of effect size seems appropriate. Further, according to a meta-analysis [26], web-based trainings for physicians achieved high-range effect sizes regarding skills (Hedges’ *g* = 0.85) and behaviors/effects on patient care (Hedges’ *g* = 0.82). Therefore, an effect size of *d* = 0.50 is expected for the primary outcome (SDM competence assessed by OPTION-12 at T_1_ adjusted for SDM competence at T_0_).

The estimation of the sample size for a covariance-analysis (ANCOVA) is comparable to an analysis of variance (ANOVA) focusing on the difference between adjusted means. A power analysis via GPower Version 3.1.2 [55] for an ANOVA (one factor with three groups: IG I, IG II, CG) was performed. The results show with a type-1 error of 5% a sample size of 159 physicians is needed to detect a statistically significant effect size of *d* = 0.50 with a power of 80%. Due to randomization issues, a sample size of 162 participants is targeted.

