#### Main hypothesis

##### Hypothesis 1

We hypothesize that in both intervention groups (IG I and II), physicians will show a higher level of external-rated SDM competence (assessed by OPTION-12 [36–38]; adjusted for T_0_) during their consultation with an SP 4 weeks after the training session (T_1_) compared to a CG (no training).

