### Statistical methods

#### Statistical analyses

To test the main *hypothesis 1* an ANCOVA is conducted. The mean of the OPTION-12 at T_1_ serves as the dependent variable and the group factor (IG I, IG II, CG) serves as independent variable. The mean of the OPTION-12 at T_0_ serves as a covariate. Post-hoc tests using a Bonferroni correction will be conducted to analyze single contrasts. To test the secondary *hypotheses 2 and 3*, two ANCOVAS and post-hoc tests, comparable to the ANCOVA for *hypothesis 1*, will be conducted with the means of the SDM-Q-9 and QQPPI at T_1_ as dependent variable, the group as independent variable and the means of SDM-Q-9 and QQPPI at T_0_ as covariates. To test *hypothesis 4* regarding the satisfaction a *t* test for independent groups with IG I and II as independent variable and the mean of the 10 general items of the training evaluation as dependent variable will be conducted. For data management and analyzing, SPSS© will be used.

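### The stated 80% power for d = 0.50 rests on a two-group effect-size conversion and on the omnibus F test, so the design does not deliver it for Hypothesis 1

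*Protocol article*

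**What the plan says.** Under Sample size, the article bases the calculation on Hypothesis 1 and its method of analysis. It states that "an effect size of *d* = 0.50 is expected for the primary outcome", and describes that outcome as "SDM competence assessed by OPTION-12 at T_1_ adjusted for SDM competence at T_0". A G*Power analysis "for an ANOVA (one factor with three groups: IG I, IG II, CG) was performed". At 5% type-1 error and 80% power the result is that "a sample size of 159 physicians is needed to detect a statistically significant effect size of" d = 0.50. The target is raised from 159 to 162 for reasons of randomization. Cohen's f, which G*Power needs for an ANOVA, is not printed. Trial design gives 54 physicians per arm.

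Under Main hypothesis, Hypothesis 1 reads that "in both intervention groups (IG I and II), physicians will show a higher level of external-rated SDM competence" than the control group (CG) at T1. Under Statistical analyses, a three-group ANCOVA with the T0 score as covariate comes first, and then: "Post-hoc tests using a Bonferroni correction will be conducted to analyze single contrasts". The number of contrasts is not given, and neither is their power.

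**The concern.** There are two separate problems. First, d describes a difference between two means and f describes the spread of all group means. The link f = d/2 belongs to two equal groups and does not carry over to three. Second, a significant three-group F test says only that the means are not all equal. It does not show that either training beats CG, still less that both do. That claim rests on the corrected contrasts, which use a stricter alpha and compare only two of the three arms.

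If both points hold, 80% is not the power for the main hypothesis. A reader who relies on it could take a non-significant contrast as evidence that a training does not work, when the chance of detecting the planned effect was little better than even.

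**Working it through.** **Inputs.** Overall alpha 0.05, target power 0.80, d = 0.50, three groups, N = 159 or 162 (Sample size); 54 per arm (Trial design); Bonferroni contrasts (Statistical analyses). As the number of contrasts is not stated, both 0.05/3 (all pairs) and 0.05/2 (each training against CG) are used, two-sided.

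**1. Reproducing 159.** One-way ANOVA power comes from the noncentral F distribution with 2 and N − 3 degrees of freedom and noncentrality λ = N·f². With f = 0.50/2 = 0.25:

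- N = 156: power 0.797
- N = 159: λ = 159 × 0.0625 = 9.94, power 0.805
- N = 162: power 0.813

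In steps of three, 159 is the first N to reach 80%. So f = 0.25 is the input that gives the published figure.

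**2. The f that d = 0.50 implies with three equal arms.** Here f is the standard deviation of the three group means in within-group SD units.

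| Means (CG, IG, IG) | f | N for 80% | Power at 159 | Power at 162 |
|---|---|---|---|---|
| 0, 0.50, 0.50 | 0.50·√2/3 = 0.236 | 177 | 75.4% | 76.2% |
| 0, 0, 0.50 | 0.236 | 177 | 75.4% | 76.2% |
| 0, 0.25, 0.50 | 0.50/√6 = 0.204 | 237 | 62.1% | 63.0% |

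The first row is the pattern in Hypothesis 1. With a largest difference of 0.50, f cannot exceed 0.236. Reaching f = 0.25 needs d = 0.25 × 3/√2 = 0.53 if both trainings are equal, or 0.25 × √6 = 0.61 if one lies midway.

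**3. Power of one training-versus-CG contrast.** Noncentral t with noncentrality 0.50 × √(54/2) = 2.60 and pooled error df = 162 − 4 = 158:

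| Two-sided alpha | Power at d = 0.50 | d detectable with 80% | Total N for 80% at d = 0.50 |
|---|---|---|---|
| 0.05/3 | 57.2% | 0.63 | 255 (85 per arm) |
| 0.05/2 | 63.2% | 0.60 | 231 (77 per arm) |
| 0.05, uncorrected | 73.3% | 0.54 | 192 (64 per arm) |

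**4. Both contrasts, or at least one.** The two contrasts share the CG, so these come from simulation (1,000,000 draws, both trainings at d = 0.50, 54 per arm). Both are significant in 41% of draws at 0.05/3 and 48% at 0.05/2. At least one is significant in 73% and 79%.

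**5. The covariate.** If d is on the T0-adjusted scale, as the text describes it, steps 2 to 4 already include the gain from ANCOVA. If d = 0.50 were instead in raw SD units with T0–T1 correlation r, the adjusted d would be 0.50/√(1 − r²). The article gives no r, so these values are assumptions:

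| r | Adjusted d | Omnibus F at 162 | One contrast, 0.05/3 | One contrast, 0.05/2 |
|---|---|---|---|---|
| 0.3 | 0.524 | 80.3% | 62.0% | 67.7% |
| 0.5 | 0.577 | 87.7% | 71.9% | 76.9% |
| 0.6 | 0.625 | 92.4% | 79.5% | 83.7% |

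**The case against.** The protocol names the three-group ANCOVA as the test of Hypothesis 1, calls the contrasts post hoc, and powers the test it names. On that view only the conversion is wrong. It costs about five points at 162 (81% to 76%), the same as needing d = 0.53 instead of 0.50. The value f = 0.25 is inferred, since no f is printed. No success rule requires both contrasts to be significant, so 41% and 48% should not be the headline. The text also does not say which SD standardises d; on the raw SD, a correlation of about 0.3 restores the omnibus test to 80%. Finally, the article calls its effect size conservative against cited effects of 0.82 to 2.11, and a detectable d of 0.60 to 0.63 is below all of these.

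Some of this stands. The conversion error alone is modest. The joint figures depend on how the hypothesis is read. The covariate argument rests on the more natural reading of the text, not on an explicit definition of the SD.

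The rest does not rescue the claim. The calculation is said to be based on Hypothesis 1, which concerns both trainings against CG, and the F test cannot establish that. Each contrast taken singly is below 80%, even uncorrected. Under the raw-SD reading an assumed correlation of 0.5 still leaves 72% to 77% per contrast. Large cited effects do not alter the power at the d = 0.50 that was planned for, and the article itself says that three of the five cited trials of non-web-based interventions had no significant comparison.

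**Conclusion.** The concern holds. The published N follows from f = 0.25, which three equal arms cannot reach when the largest difference is 0.50 SD. At 162 physicians and adjusted d = 0.50, the omnibus test has 76% power if both trainings are equally effective, and 63% if one is half as effective. Each contrast with CG has 57% (0.05/3) or 63% (0.05/2). The test that was powered accounts for more of the gap than the conversion does.

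These figures assume equal arms, complete data, two-sided contrasts and d on the baseline-adjusted scale. No drop-out allowance is stated. The planned imputation (Drop-outs and missing values) gives drop-outs in the training arms the CG change and drop-outs in CG the training change. That pulls the arms together, so drop-out would lower power further.

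**What to change.** Keep N = 162 and correct the power statement under Sample size. Suggested text, for three Bonferroni comparisons:

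> With 54 physicians per arm and d = 0.50 on the T0-adjusted scale, the omnibus F test has 76% power if both trainings exceed the control group by that amount (f = 0.236). Each Bonferroni-corrected contrast with the control group has 57% power (alpha 0.05/3); the difference detectable with 80% power is d = 0.63.

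If the correction covers only the two contrasts with CG, the last sentence should give 63%, alpha 0.05/2 and d = 0.60. The number of contrasts should be stated in either case. If d was meant on the raw SD, the article should say so and give the assumed T0–T1 correlation.

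The cost is wording, plus a less favourable stated power. No extra physicians are needed and conduct is unchanged. Holding to 80% per contrast at d = 0.50 would instead take 231 to 255 physicians.

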## Methods: Assignment of interventions

### Sequence generation

Randomization will be conducted by a computer-generated block-randomization performed by the open source randomization software Randi3 [56]. The randomization is stratified by study center and blocked into three randomization blocks (per study center) with 27 participants (nine per IG I, II and CG) to guarantee equal sample sizes in each of the three groups when targeted sample size is not achieved (2 study center × 3 randomization blocks × 3 groups × 9 participants = 162 participants).

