#### Drop-outs and missing values

Participants, who drop out after T_0_, are considered for the main outcome (OPTION-12, no missing values at T_0_ due to inclusion/exclusion criteria II and nature of external rating) according to the intention-to-treat principle using a single imputation method, in more detail we impute the mean difference of other group (MOTH-D) [57]. Therefore, the mean difference (per item) between T_1_ and T_0_ of available cases in CG is added to T_0_ of drop-outs in IG I and II and vice versa the mean difference (per item) in IG I and II is added to T_0_ of drop-outs in CG. Additionally, an analysis with available cases which completed the study (analysis per protocol) will be reported in contrast.

Missing data in the ratings of the SPs (SDM-Q-9 and QQPPI; secondary outcome) due to drop-outs will be handled like the main outcome using MOTH-D. Additionally if missing data in a single item occurs in more than 50% of all questionnaires (T_0_ and T_1_) of available cases, this item will be deleted for all SP ratings because this item does not fit into the nature of consultations in this study. It is unlikely that missing values will emerge to a greater extent as SPs were reminded frequently to complete the questionnaire completely. However, single missing values in the SDM-Q-9 and QQPPI will be not imputed. Instead, a mean value is calculated with the remaining completed items of the questionnaire.

For analyzing the training evaluation missing cases will be imputed by the worst possible mean. An analysis with available cases will be conducted and compared.

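### The sample size has no drop-out allowance, and the 80% power ignores the MOTH-D imputation, which shrinks the training effect in the primary analysis

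*Protocol article*

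**What the plan says.** The Sample size section of the protocol article bases the calculation on the main hypothesis and its method of analysis. A G*Power calculation "for an ANOVA (one factor with three groups: IG I, IG II, CG) was performed". It found that "a sample size of 159 physicians is needed to detect a statistically significant effect size of" d = 0.50 at 5% type-1 error and 80% power. The next sentence raises the number: "Due to randomization issues, a sample size of 162 participants is targeted".

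Sequence generation shows where 162 comes from: "2 study center × 3 randomization blocks × 3 groups × 9 participants = 162 participants". Under Allocation concealment mechanism, physicians are randomised after the T0 consultation, so later losses come out of the 162. The article mentions no replacement of randomised physicians.

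Drop-outs and missing values keeps physicians who leave after T0 in the primary OPTION-12 analysis: "we impute the mean difference of other group (MOTH-D"). A drop-out in IG I or IG II gets the control group's mean change added to the T0 score, and a control drop-out gets the training groups' mean change. An analysis of available cases is reported for contrast. No drop-out rate is given.

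**The concern.** The power calculation treats every randomised physician as supplying an observed T1 score. The missing-data section does not expect that, and the rule it fixes for drop-outs affects more than precision. Each drop-out is assigned the average change of the side being compared against, so if the trainings work, the analysed difference falls with every loss in any arm.

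The calculation claims to follow the method of analysis, but it describes a complete-data ANCOVA and not the primary analysis that will be run. At stake is how the result is read: a non-significant primary test would be judged against a claimed 80% power that the planned analysis may not have had.

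**Working it through.** **Inputs.** From the article: three equal arms, omnibus F test, alpha 0.05, d = 0.50 (already adjusted for T0), 162 randomised, 54 per arm. Assumed here: f = d/2 = 0.25, the conversion that reproduces the article's figure, and drop-out of 5 to 20%, unrelated to outcome.

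**1. The plan's own figure.** Noncentral F with noncentrality N × f² and 2 and N − 3 degrees of freedom:

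- N = 159: power 80.5%
- N = 162: power 81.3%

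The smallest N reaching 80% is 158, or 159 with equal arms. The stated 159 is reproduced, and 2 × 3 × 3 × 9 = 162 is correct. The surplus of 162 − 159 = 3 is all the slack there is.

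**2. What MOTH-D does to the effect.** Let D be the true difference between training and control, and p the drop-out share.

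- Equal loss in all arms: training mean (1 − p)D, control mean pD, difference (1 − p)D − pD = (1 − 2p)D.
- Loss in IG I and IG II only: training mean (1 − p)D, control unchanged, difference (1 − p)D.

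**3. How many drop-outs the surplus absorbs.** With all 162 kept and f = 0.25 × (1 − 2p):

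- 1 drop-out (p = 1/162): 80.3%
- 2 drop-outs: 79.2%
- 3 drop-outs: 78.1%

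These treat the loss as spread evenly. A single loss in one arm gives 80.5% if it is in a training arm and 79.7% if it is in the control arm. In the available-case analysis, power is 80.2% with 4 losses (N = 158) and just below 80% with 5 (N = 157).

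**4. Equal drop-out over the assumed range.**

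| Drop-out | f = 0.25(1 − 2p) | MOTH-D, formula | Available cases, N | Available cases, formula |
|---|---|---|---|---|
| 5% | 0.225 | 72.0% | 154 | 79.1% |
| 10% | 0.200 | 61.1% | 146 | 76.8% |
| 15% | 0.175 | 49.3% | 138 | 74.2% |
| 20% | 0.150 | 37.6% | 130 | 71.4% |

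**5. Simulation of the ANCOVA with MOTH-D.** The formula ignores any change in residual variance, so the analysis was also simulated: 54 per arm, 8000 runs per setting, both training arms equal, and a difference of 0.53 residual SD, which corresponds to f = 0.25.

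| Losses per arm | Share | MOTH-D power | Mean analysed effect | Available-case power |
|---|---|---|---|---|
| 3 | 5.6% | 73% | 0.47 | 79% |
| 5 | 9.3% | 64% | 0.43 | 76% |
| 8 | 14.8% | 52% | 0.37 | 74% |
| 11 | 20.4% | 36% | 0.32 | 71% |

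The table uses an assumed T0–T1 correlation of 0.5. Correlations of 0.3 to 0.7 give MOTH-D power of 72–73%, 65–67%, 52–54% and 34–37% at the two outer values. The residual SD falls only from 1.00 to 0.93–0.97 at 20% drop-out, too little to offset the smaller effect.

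**6. Loss in the training arms only.** With f = 0.25(1 − p), 10% loss gives f = 0.225 and 72.0%, and 20% gives f = 0.200 and 61.1%. Simulation comes out slightly higher, up to about 74% and 64%.

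**The case against.** Several points on the other side have weight.

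- **The arithmetic is right.** 159 and 162 both check out. The fault is a mismatch between two sections, not a miscalculation.
- **MOTH-D is a defensible conservative choice.** That stands. The point concerns a power statement that leaves it out.
- **The effect size was chosen cautiously.** The Sample size section cites effects of 0.82 to 2.11 and settles on 0.50. If both trainings truly reached 0.82, MOTH-D power would still be about 95% at 10% and 75% at 20% equal drop-out. This softens the practical consequence but does not make the claim at d = 0.50 correct.
- **The available-case analysis loses little power,** about 77% at 10%. But it is reported for contrast and is not the primary analysis.
- **Equal drop-out is an assumption.** The arms differ in burden, and loss confined to the training arms costs much less. Both patterns are therefore shown.
- **An article condenses a fuller protocol.** An allowance could be stated there, but the reason this article gives for 162 makes that unlikely.

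A reader might infer that 80% holds only with no drop-out at all, or that a true effect of the planned size will probably be missed. The documents support neither. The surplus absorbs about one loss under MOTH-D, and with equal drop-out of 5 to 10% detection remains more likely than not.

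**Conclusion.** The concern holds in this form: the sample size carries no drop-out allowance, and its 80% does not describe the primary analysis once more than about one physician drops out.

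Under equal drop-out of 5, 10, 15 and 20%, MOTH-D power is about 72–74%, 61–66%, 49–52% and 36–38%, combining the formula with simulations at correlation 0.5. Available-case power is about 79%, 77%, 73–74% and 71%. Most of the loss therefore comes from the imputation rule, not from the smaller number of physicians. With loss in the training arms only, MOTH-D power is about 72–74% at 10% and 61–64% at 20%.

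At modest drop-out, an effect of the planned size is materially less likely to be detected than claimed. At about 15% equal drop-out it is about as likely to be missed as found, and beyond that missing it becomes the likelier outcome.

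These figures assume f = 0.25, drop-out unrelated to outcome and, in the simulations, equal effects in both training arms. The drop-out rates are assumed, so the true shortfall is unknown. Whether d = 0.50 should be converted to f = 0.25 is a separate question, to be raised on its own.

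**What to change.** In the Sample size section, state an assumed drop-out rate after T0 and give the resulting power for the 162 randomised physicians. Report it for the MOTH-D primary analysis and for the available-case analysis, under equal drop-out and under drop-out in the training arms only. Say that 162 completes the randomisation blocks and contains no drop-out allowance, and do not present 80% as the power of the planned analysis when drop-outs occur.

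The cost is a few lines of text and a less favourable power statement. The design, the imputation rule and the enrolment target stay as they are.

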### Recruitment

Each study center will establish lists of physicians throughout Germany working with colon or breast cancer patients, either in cancer centers or as practitioners, by a systematic Internet research and using the lists of federal statutory physicians’ associations (Kassenärztliche Vereinigungen). We will subsequently send postal invitations to participate, provide flyers to each center’s responding practitioner and have a reference on our webpage that provides detailed information about the study. If e-mail addresses are available, we will send the invitation for participation in a digital format. Furthermore, if preferred (e.g., from a head of a cancer center), we will attend the cancer center and introduce the study and the corresponding SDM training program personally. Interested physicians are asked to contact the project team via e-mail or telephone. The responsible project team subsequently sends an e-mail including the link for the first online questionnaire to the participant and allocates a code to each participant in a consecutive numerical order.

## Methods: Assignment of interventions

### Sequence generation

Randomization will be conducted by a computer-generated block-randomization performed by the open source randomization software Randi3 [56]. The randomization is stratified by study center and blocked into three randomization blocks (per study center) with 27 participants (nine per IG I, II and CG) to guarantee equal sample sizes in each of the three groups when targeted sample size is not achieved (2 study center × 3 randomization blocks × 3 groups × 9 participants = 162 participants).

### Allocation concealment mechanism

The code of the participating physicians will be randomized after the first consultation with the SP (T_0_). For this, both study centers send the code for randomization to a study nurse per e-mail, who conducts the computer-generated randomization and informs the study centers about the result per e-mail.

### Implementation

The project team provides the result of the randomization to the participant by e-mail and coordinates the next steps in accordance to the result. For participants randomized to IG I, an appointment for the face-to-face-training is arranged, for participants of the IG II and CG an appointment for T_1_ is arranged and additionally for participants of IG II a link for the web-based interactive SDM online training is sent per e-mail.

### Blinding

Due to the nature of this trial, blinding of the physicians is not feasible. However, SPs and the independent raters, when rating the videotaped and transcribed consultations, are blinded regarding the group (IG I, IG II, CG) and the point of measurement (T_0_, T_1_).

